#### Intervention

The intervention consists in cathodal tDCS by the DC-STIMULATOR PLUS (neuroConn, Ilmenau, Germany), a CE-certified medical device, programmed to deliver either active or sham-tDCS according to a randomization 5-digit code. tDCS or sham is started as soon as possible after the inclusion, in the stroke unit or in the angiosuite during thrombectomy, in addition to reperfusion therapies. The investigator sets the cathode facing the ischemic injury (C3 or C4 according to the 10–20 system) and the anode facing the contralateral supra-orbital area (Figure 1). Then, the experimenter enters the 5-digit randomization code in the device, which blindly determines whether cathodal or sham stimulation is to be delivered, without the experimenter knowing which. Delivery of stimulation is for 20 min. Over a period of 6 h, the experimenter restarts the device every hour with the same 5-digit randomization code for another 20 min. The device delivers 1.5 mA (with 30 s for ramping up and ramping down) of cathodal direct current through the two sponge coated electrodes (electrodes size: 5 × 7 cm^2^; Figure 2). Impedance quality is obtained using saline solution and conductive gel (Elefix paste®). The device automatically checks impedance values during all tDCS sessions. In the sham condition, the device delivers 98 s of current including 30 s for ramping at the beginning and end of each session, in order to keep the blinding procedure (Figure 3). Indeed, usually, subjects feel discomfort under the electrodes during only the first few seconds or minutes of tDCS stimulation (18, 34). The experimenter notes every significant event: time of stroke onset, time of hospital arrival, time of first MRI, time of IV thrombolysis, and/or endovascular recanalization, time of each tDCS session (Figure 4).

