### Safety aspects

During the procedure, potential tDCS adverse events are checked every hour: itching, irritation, or rash, burning feelings under the electrodes, headaches, nausea, and dizziness. All these minor side events are reversible when the tDCS stops (35). To minimize these risks, a dedicated experimenter is present during each tDCS stimulation session. This experimenter asks the patient about any side-effect or discomfort and notes these data each hour. The tDCS procedure is stopped in case of adverse events.

In order to minimize the risk of rash or burning feelings, the experimenter adds saline solution and conductive gel (Elefix® paste) every hour if necessary, according to impedance values. High impedances are indeed a contributing factor for skin lesions (35). Moreover, the device automatically stops in case of impedance value superior to 15 kΩ. An independent data and safety monitoring board analyzes STICA safety data after the recruitment of 25 patients.

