#### Secondary outcomes

We defined two secondary clinical outcomes, a safety outcome and three subgroups analyses.

NIHSS: a neurological exam (with NIHSS score) is assessed at the admission and at 7 days or discharge if earlier. The difference between NIHSS score at day 7 (or discharge if earlier) and on admission constitutes the first clinical outcome assessment.Modified Rankin scale (mRs): the mRs is a 7-point disability scale ranging from 0 (no symptom) to 6 (death).The mRs is estimated at 3 months by phone interview using a simplified and standardized questionnaire (33). Whenever possible, the patient will be interviewed directly. If the patient is unable to complete the interview, the interview will be conducted based on information from the relatives or the patient's general practitioner. The mRs at 3 months constitutes the second clinical outcome assessment.

Safety outcome: safety variables, including major adverse effects (neurologic deterioration) and minor adverse effects (itching sensations, cutaneous rash, headaches, vertigo, nausea) are monitored during tDCS stimulation, and then again at day 1 and day 2.Subgroup analyses are planned according to the following stratifications: (i) patients with and without perfusion–diffusion mismatch, with hypoperfusion defined as *T*_max_ > 6 s, on admission MRI. The perfusion–diffusion mismatch is defined by the volumetric ratio between perfusion lesion (at *T*_max_ > 6 s) and diffusion lesion (ratio > 1.8). The mismatch as defined is a neuroradiological marker of the ischemic penumbra, the target of our protocol; (ii) patients with NIHSS admission score above vs. below the median NIHSS admission score; (iii) presence or absence of arterial recanalization measured by the thrombolysis in cerebral infarction scale (TICI) post-arteriography or by MR Angiography at day 1 (successful recanalization on arteriography is estimated by a TICI scale 2b or 3) and (iv) patients with and without initial large vessel occlusion. The patient population will be clearly described with respect to vessel occlusion (no vessel occlusion, otherwise site of occlusion) in further publication.

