### Statistical analysis

Continuous variables are described as mean ± standard deviation (SD) or median [interquartile range (IQR)] and are compared using the *t*-test or Mann-Whitney U-test. Categorical variables are expressed as percentages and compared using the Pearson χ^2^-test or Fisher's exact test, as appropriate. A univariate analysis is expected and adjustment is scheduled according to the success or not of recanalization. Primary outcome is analyzed in intention-to-treat, safety outcomes in per-protocol.

No intermediate analysis is planned. All data for the primary outcome will be assessed at the end of the study. The inclusion of 50 patients is planned over 30 months. This sample will allow to evaluate the feasibility of tDCS in the very acute phase of stroke and should highlight a tendency which will be used in further studies to demonstrate a statistically significant infarct growth difference between the two groups.

The number of patients (*n* = 25 per group) was empirically chosen to match the recruitment capacity of our center during the study period, and because we believe it would provide a reliable estimate of the effect size of the intervention for further studies. This planned number of patients was not based on a formal sample size calculation and we are aware that the present pilot trial will most likely be underpowered to demonstrate the superiority of the intervention over the control group with regard to the primary outcome.

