We chose to evaluate infarct growth at 24 h from stroke onset with MRI. This time point may be discussed because infarct volume may not be completely stabilized by 24 h from stroke onset. Moreover, in the DEFUSE 3 trial, with a selected population of “slow ischemic growth” (also called “slow progressors”), imaging assessment at 24 h did not show difference between groups, contrary to clinical benefit. However, vasogenic edema usually occurs in the first week and can artificially inflate lesion volume. Previous studies demonstrated that 24 h evaluation of infarct volume by non-contrast computed tomodensitometry is as well correlated to 3 month-mRS than is 1 week evaluation (59, 60). There is currently no consensus about the best time-point to evaluate infarct growth, and future stroke studies are needed to address this issue.

Despite a rigorous study protocol, there are potential drawbacks in our study. The first is the limited sample. Thus, our study will not have the statistical power to demonstrate a significant reduction in infarct growth in the cathodal tDCS group. Although limiting the number of participants is necessary in a pilot study for safety concerns, this also necessarily limits the power of efficacy assessment. If the results of our study are promising, they will be useful for the design of a phase III clinical trial with more participants. Moreover, the rationale of our study is that tDCS may act on excitotoxicity pathways in the penumbra area, blocking CSDs and PIDs until reperfusion takes place. It should however be kept in mind that the phenomenon of PIDs after stroke has only been recorded in man in malignant MCA infarction, by means of electrocorticography (17, 61–63). There is no non-invasive tool allowing the identification of CSDs and PIDs during tDCS.

In summary, STICA is underpinned by the potential of cathodal tDCS to limit excitotoxicity and ischemic damage in acute human MCA stroke, as an adjunct to standard-of-care revascularization strategies. This pilot, randomized, double-blind placebo-controlled trial will recruit 50 patients and follow them over 3 months, assessing tDCS tolerance, infarct growth, and functional outcome. Depending on the results of this pilot study, a subsequent, larger study may be planned.

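### Safety is assigned to an undefined per-protocol set while stimulation is stopped for adverse events; read in the usual way, this biases the rate of events during stimulation downward

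*Protocol article*

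**What the plan says.** The Statistical analysis section of the protocol article fixes the analysis sets in one sentence: "Primary outcome is analyzed in intention-to-treat, safety outcomes in per-protocol". The article does not define the per-protocol set and names no other set for safety.

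The Safety aspects section describes what happens during treatment: "During the procedure, potential tDCS adverse events are checked every hour". The events listed are mostly minor ones such as itching, rash, headache and nausea. The same section adds: "The tDCS procedure is stopped in case of adverse events". No severity threshold is attached.

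The Intervention section describes the full course, a first 20-min session followed by repeats: "Over a period of 6 h, the experimenter restarts the device every hour with the same 5-digit randomization code for another 20 min".

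Under Secondary outcomes, the safety variables are neurologic deterioration (major) and a list of minor effects. They "are monitored during tDCS stimulation, and then again at day 1 and day 2". The Discussion describes the trial as "assessing tDCS tolerance, infarct growth, and functional outcome".

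**The concern.** A safety set should not depend on the safety outcome. Here the event can trigger the stop, the stop makes the course incomplete, and an incomplete course ordinarily takes a patient out of a per-protocol set. The patients most informative about tolerance during stimulation would then be missing from both numerator and denominator.

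This matters because, by the article's own account, tDCS has not been used before in hyper-acute human stroke, tolerance is one of the things the trial assesses, and the comparison on infarct growth is acknowledged to be most likely underpowered. Tolerance and feasibility will therefore carry weight in any decision on a larger trial. The intention-to-treat rule in the same sentence covers only the primary outcome, so it gives no protection to safety.

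**Working it through.** **The plan's own figure.** The article gives no expected adverse-event rate, stopping rate or safety precision, so there is no safety figure to reproduce. Its sample-size figures concern infarct growth and do not bear on this point.

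**Inputs from the article**
- Group size: 25 per arm (Statistical analysis).
- Full course: hourly 20-min sessions over 6 h (Intervention).
- Stop for adverse events, no threshold (Safety aspects).
- Safety window: during stimulation, day 1 and day 2 (Secondary outcomes).
- Sham: 98 s of current per session (Intervention).

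**Inputs assumed**
- *p*, the true proportion of patients with an event during stimulation: 10% to 40%.
- *c*, the share of those patients who are stopped and excluded: 0.5 or 1.
- Per-protocol means that the full course was completed.

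**Step 1: rate within one arm.** Excluding a share *c* of the patients with an event leaves *p*(1 − *c*) with an event among 1 − *pc* patients, so the per-protocol rate is *p*(1 − *c*)/(1 − *pc*). This is below *p* whenever *c* > 0 and 0 < *p* < 1.

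| True rate *p* | *c* = 0.5: reported | Expected exclusions of 25 | *c* = 1: reported | Expected exclusions of 25 |
|---|---|---|---|---|
| 10% | 5.3% | 1.25 | 0% | 2.5 |
| 20% | 11.1% | 2.5 | 0% | 5 |
| 30% | 17.6% | 3.75 | 0% | 7.5 |
| 40% | 25.0% | 5 | 0% | 10 |

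In counts: 6 of 25 patients have an event (24%) and 4 of the 6 are stopped and excluded. The reported rate is (6 − 4)/(25 − 4) = 2/21 = 9.5%.

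**Step 2: events after stimulation.** The table covers only events that arise during stimulation. Suppose six of 25 patients are stopped for such an event and two others, with completed courses, have a first event at day 1 or day 2. The all-treated rate is 8/25 = 32%. The per-protocol rate is 2/(25 − 6) = 2/19 = 10.5%. It is too low, but not zero.

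**Step 3: between arms.**
- Equal events and equal stops: 6/25 in each arm with 4 excluded in each gives 2/21 against 2/21. Both rates are too low, but the difference stays at zero, as it should.
- More stops in the active arm: 6/25 active against 3/25 sham is 24% − 12% = 12 percentage points. With 4 active and 2 sham patients excluded, it becomes 2/21 (9.5%) against 1/23 (4.3%), about 5 points.
- Extreme case: 6/25 active against 0/25 sham has a two-sided Fisher exact p of 0.022. If all six are stopped and excluded, the table is 0/19 against 0/25 and no signal remains.

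All counts in steps 1 to 3 are illustrations. The direction within an arm follows from the exclusion itself. The direction between arms depends on where the stops fall.

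**The case against.** The strongest objection is that the exclusion is inferred. The article does not define per-protocol or make completion of all sessions a condition. A patient stopped under the protocol's own rule was arguably treated according to protocol, and set definitions are often left to a full protocol or SAP that is not shown here. If the authors meant all patients treated, by treatment received, the problem disappears. This stands as a limit on certainty. It does not rescue the sentence, which chooses per-protocol in contrast to intention-to-treat, while nothing in the article keeps stopped patients in.

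A reader might also infer more than the article supports:

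- **That every harmed patient is removed, or that the safety rate must come out at zero.** Safety is also assessed at day 1 and day 2, and an event first seen after a completed course cannot have caused a stop. The zero applies only to events during stimulation, and only if every such patient is stopped and excluded.
- **That the comparison is certainly biased in favour of tDCS.** The stopping rule applies to both arms, and sham also delivers some current. More stops in the active arm are plausible, because sham gives only 98 s per session, but the article does not say so.
- **That impedance cut-outs are a second route to exclusion.** The article says "the device automatically stops in case of impedance value superior to 15 kΩ" and calls high impedance a contributor to skin lesions. It also has saline and gel added according to impedance values, and nothing says that a cut-out ends the patient's course.
- **That the monitoring board's review after 25 patients is affected.** Nothing ties that review to the per-protocol set.

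It can also be said that safety is a secondary outcome and that events are noted hourly whatever set is used. Both are true. The second means that the problem can be repaired without loss of data.

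**Conclusion.** The point holds in a limited form. The article names a per-protocol safety analysis and also a rule that stops stimulation for adverse events. Under the usual meaning of per-protocol, membership of the safety set would depend in part on the safety outcome, and the reported rate of events during stimulation would be too low in any arm with such stops. Bias in the between-arm comparison needs the further condition that more active than sham patients are stopped.

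The size is unknown. If half of the patients with an event are stopped and excluded, assumed true rates of 10% to 40% would appear as 5.3% to 25.0%. The conclusion rests on two assumptions: that per-protocol means completing the course, and that at least some patients are stopped for an event.

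**What to change.** In the Statistical analysis section, replace the clause on safety with a rule of this kind: safety outcomes are analysed in all randomised patients in whom any stimulation, active or sham, was started, grouped by the stimulation actually received, whatever the number of sessions completed. Add that early stops are reported by arm with their reasons. Any per-protocol safety table should be labelled supplementary.

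The cost is a sentence or two. Events are already noted hourly and the time of each session is already recorded, so no new data are needed. The downside is a possibly less favourable adverse-event rate. The clinical stopping rule is not touched. If the authors already intended an all-treated set, the change is only a clarification.

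The definition should be settled before unblinding, so that the choice of set cannot be influenced by the results.

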In order to inform sample size and power calculations, we have used unpublished data from 200 consecutive patients who underwent mechanical thrombectomy for acute ischemic stroke in our institution and for whom infarct growth between admission and 24 h follow-up imaging was estimated using the method described in section Primary Outcome (voxel-wise infarct growth on DWI). These data were used to confirm the log-normal distribution of infarct growth and to provide the expected median and SD for the control group of STICA, namely 16 and 48.8 ml, respectively. Using the method described by O'Keeffe et al. (41), and assuming a 30% relative reduction in median infarct growth in the treatment group, 177 patients per group would be needed (two-sided comparison of untransformed medians, alpha = 5%, beta = 20%). Based on this effect size, a sample size of 25 patients per group would yield a statistical power of 18%. Conversely, with 25 patients per group, the effect size that could be detected with a statistical power equal to 80% would be a 65% relative reduction in infarct growth. Such an effect size may seem overly optimistic but the main aim of this pilot study is to provide a reasonable estimate of infarct growth reduction with cathodal tDCS, in order to inform the sample size calculation for, and feasibility of a multicenter phase IIb or phase III superiority trial.

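### On the plan's own inputs, 25 patients per group cannot give the reliable effect-size estimate that is offered as a reason for the sample size

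*Protocol article*

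**What the plan says.** All of this stands in the Statistical analysis section of the protocol article, apart from the Discussion sentence quoted last.

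- Origin of the number: "The number of patients (*n* = 25 per group) was empirically chosen to match the recruitment capacity of our center". The second reason given is that "we believe it would provide a reliable estimate of the effect size of the intervention for further studies".
- Use of the result: the sample "should highlight a tendency which will be used in further studies to demonstrate a statistically significant infarct growth difference between the two groups".
- Purpose: after reporting low power, the section says that "the main aim of this pilot study is to provide a reasonable estimate of infarct growth reduction with cathodal tDCS", so as to inform the sample size and feasibility of a multicentre phase IIb or III trial.
- Inputs: institutional data on 200 thrombectomy patients. On the shape of the outcome: "These data were used to confirm the log-normal distribution of infarct growth". The control-group values taken from the same patients are a median of 16 ml and an SD of 48.8 ml.
- Results from those inputs: 177 per group for a 30% reduction in the median (two-sided 5%, 80% power), 18% power at 25 per group, and a 65% reduction detectable with 80% power at 25 per group.
- Discussion: "If the results of our study are promising, they will be useful for the design of a phase III clinical trial".

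The section says openly that no formal calculation set the number and that the trial is most likely underpowered for superiority. It gives no expected interval width for the estimate that it calls the main aim.

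**The concern.** Reliability of the estimate is one of the two reasons given for 25 per group, and the estimate is what the pilot is meant to hand on. Power and precision both follow from the same standard error. A design with 18% power at the assumed effect therefore cannot also estimate that effect reliably. If planners of the later trial take the wording at face value and treat the observed reduction as a sound planning value, that trial could be far too small or needlessly large.

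**Working it through.** **Inputs** (Statistical analysis section): control median 16 ml; SD 48.8 ml; log-normal distribution; ratio of medians 0.70 (16 to 11.2 ml); two-sided alpha 5%; power 80%; 25 per group.

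**1. Log-scale variance.** For a log-normal variable with median m and log variance v, SD² = m²·e^v·(e^v − 1), so e^v = [1 + √(1 + 4·SD²/m²)]/2.
- Control: SD²/m² = (48.8/16)² = 9.3025, e^v = 3.591, v = 1.278 (log-SD 1.13).
- Treated, same raw SD of 48.8 ml: (48.8/11.2)² = 18.985, e^v = 4.886, v = 1.586.
- Sum V = 2.865.

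**2. Reproducing the article's figures.**
- n per group = (1.960 + 0.842)²·V/(ln 0.70)² = 7.849 × 2.865/0.1272 = 176.7, so 177 (stated 177).
- Power at 25 per group: standard error = √(2.865/25) = 0.339; 0.357/0.339 = 1.054; Φ(1.054 − 1.960) ≈ 0.18 (stated 18%).
- Detectable effect: a 65% reduction puts the treated median at 5.6 ml with v = 2.222. The standard error is √(3.501/25) = 0.374, and Φ(1.050/0.374 − 1.960) = 0.80 (stated 65%).

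The same raw SD in both arms is thus the reading behind all three figures.

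**3. Precision at 25 per group.**
- The standard error of 0.339 compares with an assumed log effect of 0.357.
- 95% interval factor: exp(1.96 × 0.339) = 1.94. With a common log-SD of 1.13 in both arms, the standard error is √(2 × 1.278/25) = 0.320 and the factor is 1.87.
- Expected interval at a true ratio of 0.70: 0.70/1.94 = 0.36 to 0.70 × 1.94 = 1.36, that is, from a 64% reduction to a 36% increase. It contains every infarct reduction cited from the rodent studies in the Discussion (20% to 37%), no effect, and harm.
- Probability that the estimate points the wrong way: Φ(−0.357/0.339) = 0.146.

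**4. What plugging in would do** (an assumption, since the article does not state this method). Set the next trial's n as 7.849 × 2.865/(estimated log ratio)², with V held at its planning value.
- Quartiles of the estimated log ratio: −0.357 ± 0.6745 × 0.339 = −0.585 and −0.128 (ratios 0.557 and 0.880).
- n per group at the quartiles: 22.48/0.585² ≈ 66 and 22.48/0.12836² ≈ 1,365, against 177 needed. Simulating 200,000 pilots with the variances also estimated gives about 64 and 1,314.
- n falls within 50% of 177 when the log reduction lies between 0.357/√1.5 = 0.291 and 0.357/√0.5 = 0.504. The probability is Φ(0.193) − Φ(−0.436) = 0.245, about one pilot in four.

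**5. What the pilot estimates better.** A pooled log-SD on 48 degrees of freedom has 95% limits √(48/69.0) = 0.83 and √(48/30.8) = 1.25 times the estimate, that is −17% to +25%. This assumes a common log-scale SD. Since n is proportional to the variance, it moves n by a factor of about 0.70 to 1.56.

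**6. Sensitivity to covariate adjustment.** The planned adjustment for recanalization could narrow the interval, but the article gives no figure. If it removed 30% or 50% of the log variance (assumed values), the interval at a true ratio of 0.70 would be 0.40 to 1.22 or 0.44 to 1.12.

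**The case against.** The best defence is disclosure. The article says that the number is empirical and the trial underpowered, reports 18% power, calls a 65% reduction possibly too optimistic, and lists the limited sample as its first drawback. A statistician can recover the standard error from those figures. The claim of reliability is introduced as a belief, and a later sentence softens it to a reasonable estimate. At a true 30% reduction, about 85% of pilots would still point the right way.

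The disclosure is real, but it concerns testing. The section concedes low power and then presents the estimate as what the pilot can deliver all the same. Both rest on the same standard error, so the concession does not rescue the claim.

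The defence is right on three stronger readings that a reader might be tempted by:
- *The next trial will be sized by plugging in the observed effect, or launched or abandoned on its direction.* The article says only that the estimate will inform the calculation and that a larger study may follow, depending on results that include tolerance and functional outcome. The sentence about a tendency comes closest, but it names no method.
- *The lack of a numeric meaning for promising is a defect.* Progression criteria are commonly left to the full protocol or analysis plan, which are not shown.
- *The sample-size arithmetic is wrong.* It reproduces.

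**Conclusion.** The claim of a reliable effect-size estimate is wrong as written. On the article's inputs, the standard error nearly equals the assumed effect, and the 95% interval spans a factor of about 1.9 either way. The conclusion does not turn on the variance model (factor 1.94 or 1.87), and it survives an adjustment that removes half the log variance.

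It rests on the log-normal model and on a variance taken from thrombectomy patients only. The trial also enrols patients given thrombolysis alone, so the true spread may be larger or smaller. The range of 66 to 1,365 per group shows what plugging in would do; it does not describe a rule in the article. Feasibility, safety and variance remain sound aims for 50 patients.

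**What to change.** Keep 25 per group and change the text of the Statistical analysis section:

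1. Replace the claims of a reliable and a reasonable estimate by the expected precision: a 95% interval of the estimate times or divided by about 1.9, with the variance assumption stated.
2. State that the later trial will be sized on a pre-set worthwhile reduction (for example the 30% already used in the article's own calculation).
3. State that the pilot supplies feasibility, safety and the log-scale SD, and give the uncertainty of that SD (about −17% to +25%).
4. State that the observed effect will be reported with its confidence interval and will not be plugged in as the planning effect. Reword the sentence about a tendency to match.

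The cost is a change of wording, with no extra patients and no new data. The drawback is that the stated precision looks less favourable than the present text suggests.
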